##### Strategies to improve adherence to intervention protocols

Adherence to the intervention protocol depends primarily on the treating physicians. The study team including intensive care physicians, nephrologists, and hepatologists will be responsible for monitoring protocol adherence. Most importantly, study physicians will oversee timely exchange of the CytoSorb adsorbers and timely blood sample collections. Additional treatment of the patients will be independent from the study interventions and based on well-established treatment standards and standard operating procedures that are followed by the treating physicians.

##### Relevant concomitant care and interventions that are permitted or prohibited during the trial

Besides CRRT and cytokine adsorption in the CRRT with CytoSorb and the CRRT without CytoSorb groups and collection of study-associated additional blood samples, the treatment of the patients will follow established standards. There are no specific interventions that are prohibited during the trial.

#### Outcomes

##### Primary endpoint

The primary endpoint is serum bilirubin level after 72 h. The reference time (*t*_0_) is the start of cytokine adsorption in the CRRT with the CytoSorb group and the start of CRRT in the CRRT without the CytoSorb group. In the no CRRT group, the reference time (*t*_0_) will be the time of randomization plus 2 h (since this is the expected average duration between randomization and initiation of CRRT in the CRRT groups).

##### Secondary endpoints

Survival time (days) from baselineInterleukin-6 after 72 hLiver function parameters (72 h): Quick/INR, AST, ALT, AP, g-GTBlood lactate (72 h)Clinical scores: CLIF-SOFA-score [38], MELD score [39], SOFA score [40], SAPS II [41], and FIPS score [42] (72 h)Ventilator-free days (VeFD) in the first 30 days after randomization, where each day on invasive mechanical ventilation (IMV), non-invasive ventilation (NIV), or ECMO is defined as ventilator day. VeFD=0 if the patient dies in the first 30 days after randomizationVasopressor free days (VaFD) in the first 30 days after randomization, where each day with any dose of epinephrine, norepinephrine, dobutamine, argipressin or terlipressin is defined as vasopressor day. VaFD=0 if the patient dies in the first 30 days after randomizationDialysis-free days (DFD) in the first 30 days after randomization, where each day on renal replacement therapy (RRT) is defined as dialysis day. DFD=0 if the patient dies in the first 30 days after randomizationA biomarker panel of pro- and anti-inflammatory cytokines (blood samples will be frozen and stored for later analyses, the panel will be determined at the time of analysis)

Mean serum bilirubin levels and clinical scores at 72 h will be compared between treatment groups. Medians will be compared for other laboratory outcomes at 72 h. Survival times will be compared based on estimated hazard ratios and inspection of Kaplan-Meier curves. VeFD, VaFD, and DFD will be summarized by medians and compared between treatment arms based on the estimated probability of a better outcome (C-Index).

The primary endpoint and the secondary endpoints were selected for their relevance in the context of ACLF. Bilirubin is a core parameter describing disease severity and progression in ACLF. Bilirubin measurements are widely available. Previous retrospective analyses of patients with ACLF treated with CytoSorb described the course of bilirubin and these findings could therefore be used for the sample size estimation for this trial.

Interleukin-6 has previously been described as a prognostic factor in the context of the systemic inflammation hypothesis for ACLF. Liver function parameters, such as Quick/INR, AST, ALT, AP, g-GT are widely accepted routine parameters for the assessment of liver function, The CLIF-SOFA-Score, the MELD score, and the FIPS score are well-established scores for the assessment of liver disease severity. Blood lactate, VeFD, VaFD, and DFD describe disease severity and required treatment intensity for ICU patients. Finally, the SOFA score and SAPS II are well-established scoring systems for the assessment of disease severity of ICU patients.

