### Data collection, management, and analysis

#### Data collection methods

##### Clinical data

Besides patient-specific demographic and personal data (e.g., age, height) medical pre-conditions, previous treatment in another hospital before referral to the Freiburg University Medical Center, and previous medication will be documented. Beyond this, during the study, clinical- and treatment-related data will be collected, including information on oxygen demand and ventilation parameters in patients requiring mechanical ventilation or high-flow oxygen support (see Table 2 for details) and clinical scores will be assessed at baseline and at 72 h (CLIF-SOFA-score [38], MELD score [39], SOFA score [40], SAPS II [41] and FIPS score [42]). Survival from baseline up to day 90 will be assessed for all patients. All clinical data will be retrieved from the electronic patient files (MEONA GmbH, Freiburg, Germany and COPRA System GmbH, Berlin, Germany). All clinical information collected for this study will be available from the electronic patient charts.

**Table 2 Tab2:** Clinical data collected during the study. Data will be retrieved from the hospital’s electronic patient charts

	0 h	6 h	12 h	24 h	48 h	72 h	7 days
Supply of red cell concentrates [number]	x	x	x	x	x	x	x
Supply of thrombocyte concentrates [number]	x	x	x	x	x	x	x
Supply of fresh frozen plasma [number]	x	x	x	x	x	x	x
Dosage of norepinephrine [μg/kg/min]	x	x	x	x	x	x	x
Dosage of dobutamin [μg/kg/min]	x	x	x	x	x	x	x
Dosage of epinephrine [μg/kg/min]	x	x	x	x	x	x	x
Dosage of argipressin [IE/kg/min]	x	x	x	x	x	x	x
Dosage of terlipressin [mg/h]	x	x	x	x	x	x	x
Oxygen supply (l/min)	x	x	x	x	x	x	x
In patients requiring mechanical ventilation:							
FiO_2_	x	x	x	x	x	x	x
PEEP [mbar]	x	x	x	x	x	x	x
Body temperature	x	x	x	x	x	x	x
RRsys [mmHg]	x	x	x	x	x	x	x
RRdia [mmHg]	x	x	x	x	x	x	x
Mean arterial pressure [mmHg]	x	x	x	x	x	x	x
Heart rate [1/min]	x	x	x	x	x	x	x

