#### Statistical methods

##### Statistical methods for analyzing primary and secondary outcomes

Confirmatory statistical testing will be restricted to the analysis of the primary outcome, to be followed by descriptive reporting of other trial results**.** Emphasis will be given to reporting of effect estimators with two-sided 95% confidence intervals rather than *p* values, which will be considered statistically significant if below 5% for tests of equality.

In the primary analysis, randomized groups will be compared using a sequential closed test procedure: To guarantee a multiple significance level of 5%, confirmatory statistical testing at nominal significance level *α*=5% will continue until the first non-significant result, followed by descriptive reporting of the results of subsequent analyses. Treatment arms will be compared in the following order: CRRT with CytoSorb versus CRRT without CytoSorb, CRRT without CytoSorb versus no CRRT, CRRT with CytoSorb versus no CRRT.

The effects of CRRT with CytoSorb versus CRRT without CytoSorb with respect to the primary endpoint serum bilirubin level after 72 h will be estimated and tested within a linear regression model, and the two-sided 95% confidence interval will be calculated. The model will include randomized treatment group and continuous baseline bilirubin level as independent variables. Robust standard errors will be used to allow for different error variability in the two treatment groups. The two-sided test for a difference between the interventions CRRT with CytoSorb and CRRT without CytoSorb at significance level 5% will be based on the two-sided 95% confidence interval from the linear regression model. This is expected to increase the power compared to a t-test, due to adjustment for baseline bilirubin level. The same modeling approach will be employed for the comparisons of CRRT without CytoSorb versus no CRRT and CRRT with CytoSorb versus no CRRT, respectively.

No interim analysis will be performed for the primary endpoint. Before the end of the study and enrollment of all participants, no early confirmatory conclusion of the superior efficacy of the study intervention can be drawn.

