Another important secondary aspect of the trial is the preparation of translational research into the mechanism of action induced by cytokine adsorption. To this end, an exploratory analysis of a broad array of clinical and inflammatory parameters with a potential role in ACLF will be performed. Statistical analysis will be designed to identify those parameters that are most clearly affected by cytokine adsorption. The primary focus will be on patients randomized to CRRT with CytoSorb and CRRT without CytoSorb. During initial data analysis, a pre-specified set of monotone transformations will be applied to the 72 h measurements of each parameter in the array, with the aim to reduce skewness. The skewness of the transformed values will be calculated for each parameter and each transformation. Among the transformations considered, the one yielding the mean skewness closest to zero, averaging skewness over parameters, will be selected and applied to both baseline and 72 h measurements of each parameter. For each parameter, the effects of CRRT with CytoSorb versus CRRT without CytoSorb with respect to the change from baseline (transformed value after 72 h minus transformed value at baseline) will be tested within a linear regression model including treatment and the transformed baseline value as independent variables. Robust standard errors will be used to allow for different error variability in the two treatment groups. The two-sided p-values based on these linear regression models will be adjusted for multiple testing using the Benjamini-Hochberg method to control the False Discovery Rate of parameters claimed to differ between treatments at the 5% level [43, 44].

Descriptive analyses of the remaining secondary endpoints will be performed with regression models or statistical tests as appropriate for the respective type of data.

For safety reasons, mortality will be closely monitored throughout the trial. Criteria for early termination of the study are listed and explained in the “Early termination of the study” section.

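### For the 72-h liver tests and clinical scores (and IL-6, if outside the exploratory array) the protocol names only medians or means and commits to no baseline-adjusted analysis

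*Protocol article*

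**What the plan says.** The Secondary endpoints section names the comparison for each type of outcome. For scores it reads "Mean serum bilirubin levels and clinical scores at 72 h will be compared between treatment groups", and for the remaining laboratory values "Medians will be compared for other laboratory outcomes at 72 h". No baseline value is mentioned in either sentence.

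The section on statistical methods for primary and secondary outcomes contains three further rules:

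- Primary endpoint (bilirubin): "The model will include randomized treatment group and continuous baseline bilirubin level as independent variables". The reason given is "This is expected to increase the power compared to a t-test, due to adjustment for baseline bilirubin level".
- Exploratory array: "an exploratory analysis of a broad array of clinical and inflammatory parameters with a potential role in ACLF will be performed". Each member's transformed change from baseline "will be tested within a linear regression model including treatment and the transformed baseline value as independent variables". The members are not listed.
- Everything else: "Descriptive analyses of the remaining secondary endpoints will be performed with regression models or statistical tests as appropriate for the respective type of data".

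The baseline data are planned. The Clinical data section says that "clinical scores will be assessed at baseline and at 72 h", naming CLIF-SOFA, MELD, SOFA, SAPS II and FIPS. Table 3 schedules IL-6, INR, AST, ALT, AP and g-GT at 0 h and 72 h. Lactate is not in Table 3. It is listed among the blood gas parameters, which the Blood samples section expects to be incomplete in the no CRRT group.

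**The concern.** The protocol gives baseline adjustment to the primary endpoint and to an unlisted exploratory array, but not in so many words to the named secondary endpoints between them. Someone who follows the Secondary endpoints section as written would compare 72-h medians of INR, AST, ALT, AP and g-GT and 72-h means of five scores, leaving the matching 0-h values unused. No reason for the different treatment is given.

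At stake is the width of the intervals. The plan puts its emphasis on effect estimates with 95% confidence intervals, and with 17 patients per arm those intervals are wide. Randomisation is stratified on baseline bilirubin only, so chance differences in the other variables are left to the analysis.

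IL-6 has a problem of its own. If it belongs to the array, the document gives it two analyses with different targets: a 72-h median comparison and an adjusted mean change on a transformed scale. If it does not, it is in the same position as the liver tests.

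**Working it through.** **Inputs.** From Sample size: 17 per arm, two-sided 5%, difference 5 mg/dl, SD 5 mg/dl, power 80%. Assumed, because the documents give none: correlation r between the 0-h and 72-h values of the same variable, taken as 0.3 to 0.8. All 17 patients per arm are taken to have both values.

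**The plan's own figure.** Two-group t-test, standardised difference 5/5 = 1, noncentrality √(17/2) = 2.92, 32 degrees of freedom: power 80.7%. With 16 per arm it is 78.1%. The stated 17 per arm and 80% reproduce. This applies to bilirubin; no power is stated for the secondary endpoints.

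**Gain from adjustment.** Adjusting for the 0-h value multiplies the residual variance by (1 − r²). Estimating the slope under chance baseline imbalance costs a factor of 1 + 1/(2n − 4) = 1 + 1/30 = 1.033, and one degree of freedom is lost.

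- SE ratio, adjusted to unadjusted = √[(1 − r²) × 1.033]
- Equivalent unadjusted patients per arm = 17 / [(1 − r²) × 1.033]

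| r | 1 − r² | SE ratio | SE reduction | Equivalent n per arm | Power for a 1 SD difference |
|---|---|---|---|---|---|
| none | 1 | 1 | – | 17 | 0.81 |
| 0.3 | 0.91 | 0.97 | 3% | 18 | 0.83 |
| 0.5 | 0.75 | 0.88 | 12% | 22 | 0.89 |
| 0.7 | 0.51 | 0.73 | 27% | 32 | 0.97 |
| 0.8 | 0.36 | 0.61 | 39% | 46 | 0.996 |

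The last column borrows the 1 SD difference from the bilirubin calculation for illustration only.

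**Medians.** In a simulation with normal data (8,000 runs, 17 per arm), the difference in medians had a standard deviation of 0.42 to 0.43 SD units, the difference in means 0.34, and the adjusted difference 0.33, 0.30 and 0.25 at r = 0.3, 0.5 and 0.7. The efficiency of medians relative to means is about (0.34/0.42)² ≈ 0.65. This holds for near-normal data, so for a skewed laboratory value it applies on a scale where the value is roughly symmetric.

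**Chance imbalance.** The standard error of a baseline difference is √(2/17) = 0.34 SD. For a variable unrelated to bilirubin, an imbalance above 0.5 SD lies 0.5/0.343 = 1.46 standard errors out and arises in about 14% of trials.

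**The passages side by side.** Bilirubin shares a sentence with the scores in Secondary endpoints and then receives a named adjusted model. The scores and liver tests receive none by name. They are either members of an array that is not listed or fall under the clause that leaves regression or tests open.

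**The case against.** The strongest reply is that Secondary endpoints names summary measures, not models. Bilirubin appears there as a comparison of means and is later adjusted for baseline; survival appears as a hazard ratio and later becomes a Cox model with baseline bilirubin. Silence about baseline in that section therefore does not mean that no adjustment is planned. IL-6 is an inflammatory parameter and the scores are clinical ones, so both may sit in the adjusted array. The open clause permits regression, and covariates for descriptive endpoints are often settled in an analysis plan, which is not shown here.

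Much of this stands. A reader might infer that the plan compares raw values and discards the 0-h data; the documents do not say so. A reader might also infer that the estimates would be biased by chance imbalance. Under randomisation they are not, and their confidence intervals already allow for such imbalance. Nor can a loss of planned power be claimed. Confirmatory testing is restricted to the primary outcome, and no effect size or test is stated for these endpoints. A figure such as 42% power for comparing medians needs an assumed 0.8 SD effect and a test of medians that the protocol does not name.

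What the reply does not remove is that the only comparison stated for these endpoints by type is a 72-h median or mean. The overriding model is named for bilirubin alone, membership of the array is unstated, and the open clause permits an unadjusted test as readily as a regression.

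**Conclusion.** The point holds as a gap in commitment with a cost in precision. For INR, AST, ALT, AP, g-GT and the five scores, and for IL-6 if it is outside the array, the protocol does not commit to using the 0-h value, although it schedules that value and credits adjustment with added power elsewhere.

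If the comparison is unadjusted, its standard error exceeds what the same data would allow. Adjustment would cut it by about 3, 12 or 27% at correlations of 0.3, 0.5 or 0.7, and a comparison of medians would be less precise still for near-normal data. The size rests wholly on the assumed correlation, and at the low end it is negligible. The endpoints are descriptive, so no confirmatory conclusion depends on this.

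Lactate has to be left out of the general claim, because its 0-h value is not assured.

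**What to change.** State that IL-6, INR, AST, ALT, AP, g-GT and each clinical score at 72 h will be compared by linear regression on treatment and the same variable at 0 h, on a log or other transformed scale where skewed, with robust standard errors as in the primary model. Report an adjusted difference or ratio with its 95% confidence interval. Keep 72-h medians and means as descriptive summaries.

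List which endpoints belong to the exploratory array. On the same scale this causes no conflict: with the 0-h value as covariate, modelling the 72-h value or the change from baseline gives the same treatment effect, because subtracting the baseline only lowers its own coefficient by 1.

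For lactate, apply the model only where a 0-h value exists and report how many patients per arm that leaves.

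The cost is two or three sentences and one degree of freedom per model. No new data are needed for the endpoints scheduled at 0 h. For lactate, adjustment may lose patients in the no CRRT group.

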##### Safety endpoints

Assessment of adverse (device) effects (A(D)E)), serious adverse (device) effects SA(D)E, unanticipated serious adverse device effects (USA(D)E)), device deficiencies (DD) and (serious) incidents during the study period. Proportions of patients with the respective incidents will be reported.

#### Participant timeline

The participant timeline is shown in Fig. 3.

**Fig. 3 Fig3:**
[figure not shown]
Participant timeline displaying timepoints of interventions and assessments during the 30-day study period. After the end of study (day 30) survival of the study participants will be followed up until day 90. CS, CytoSorb

#### Schedule of enrollment, interventions, and assessments

The schedule of enrollment, interventions, and assessments is shown in Table 1.

**Table 1 Tab1:**
[figure not shown]
Schedule of enrollment, interventions, and assessments, tabular view

#### Sample size

In this study, the randomization to the treatment arms CRRT with CytoSorb, CRRT without CytoSorb, and no CRRT will be done with a 1:1:1 ratio. The group with no CRRT is included merely for exploratory analysis of safety aspects and does not affect the power analysis. The sample size calculation is motivated by data from case reports and retrospective case series, according to which serum bilirubin levels in patients with liver failure could be reduced by 50% by adsorption in the CytoSorb adsorber for 72 h [17–20]. We expect a mean of 10 mg/dl serum bilirubin at baseline, no change in control patients, and a reduction to a mean of 5 mg/dl after 72 h in the cytokine adsorption group. The typical range, 1 to 20 mg/dl, implies an expected standard deviation of about 5 mg/dl. This is a conservative estimate, as the inclusion criterion, bilirubin >5mg/dl, was not considered for the calculation. On the basis of a two-group *t*-test with a two-sided significance level of 5%, a sample size of 17 patients in each group yields a power of 80% to detect a difference if it is assumed that the mean serum bilirubin levels after 72 h differ by 5 mg/dl, given a standard deviation of 5 mg/dl in both groups. This is conservative in that we anticipate a lower standard deviation after 72 h in the intervention group. No missing values up to 72 h are expected. Hence, the numbers of patients to be randomized to the three treatment arms are *n*=17:17:17.

In the unexpected event that patients die within the study before reaching the 72-h end point, we will describe an appropriate expansion of enrolment in an amendment to this study protocol.

#### Recruitment

Patients with ACLF and AKI KDIGO stage 3 treated at the University of Freiburg Medical Center will be eligible for study participation. Patients meeting the inclusion criteria (or a legally authorized representative) will be asked for study participation and exclusion criteria will be assessed. All patients will be recruited by ASe, DB, or ASu. The first patient was recruited on December 7, 2021. Based on a retrospective analysis of patient records at our center, we expect about 50 patients per year meeting the inclusion criteria for this study.

### Assignment of interventions

#### Allocation

##### Sequence generation

Allocation to the intervention and control groups is carried out by 1:1:1 randomization, stratified for baseline serum bilirubin level (< 10 mg/dl, ≥ 10 mg/dl) and with blocks of variable length within strata. The block lengths will be documented separately and will not be disclosed to the investigators. Staff not otherwise involved in the trial will provide a computer-generated random list with the allocation sequence for the study groups.

##### Concealment mechanism

Allocation concealment will be ensured via an online randomization service (“The Randomizer”: www.randomizer.at). The random list will not be accessible to the clinical study team.

##### Implementation

When a patient with ACLF is selected for potential study inclusion a member of the study team will be informed. After assessment of inclusion and exclusion criteria informed consent will be obtained from the patient or from a legally authorized representative (see section 7.3. for details). Then a member of the study team will request online randomization according to the patient’s baseline bilirubin subgroup. When randomization results in “CRRT with CytoSorb” or “CRRT without CytoSorb” a CRRT machine will be ordered from the dialysis nurse on call and connected to the patient blood circuit, with or without a CytoSorb adsorber, respectively. If randomization results in “no CRRT” the patient will not receive early CRRT.

#### Blinding (masking)

The trial is an open-label trial, therefore, there is no blinding, neither for participants nor for the care providers or the study team.

### Data collection, management, and analysis

#### Data collection methods

##### Clinical data

Besides patient-specific demographic and personal data (e.g., age, height) medical pre-conditions, previous treatment in another hospital before referral to the Freiburg University Medical Center, and previous medication will be documented. Beyond this, during the study, clinical- and treatment-related data will be collected, including information on oxygen demand and ventilation parameters in patients requiring mechanical ventilation or high-flow oxygen support (see Table 2 for details) and clinical scores will be assessed at baseline and at 72 h (CLIF-SOFA-score [38], MELD score [39], SOFA score [40], SAPS II [41] and FIPS score [42]). Survival from baseline up to day 90 will be assessed for all patients. All clinical data will be retrieved from the electronic patient files (MEONA GmbH, Freiburg, Germany and COPRA System GmbH, Berlin, Germany). All clinical information collected for this study will be available from the electronic patient charts.

**Table 2 Tab2:** Clinical data collected during the study. Data will be retrieved from the hospital’s electronic patient charts

	0 h	6 h	12 h	24 h	48 h	72 h	7 days
Supply of red cell concentrates [number]	x	x	x	x	x	x	x
Supply of thrombocyte concentrates [number]	x	x	x	x	x	x	x
Supply of fresh frozen plasma [number]	x	x	x	x	x	x	x
Dosage of norepinephrine [μg/kg/min]	x	x	x	x	x	x	x
Dosage of dobutamin [μg/kg/min]	x	x	x	x	x	x	x
Dosage of epinephrine [μg/kg/min]	x	x	x	x	x	x	x
Dosage of argipressin [IE/kg/min]	x	x	x	x	x	x	x
Dosage of terlipressin [mg/h]	x	x	x	x	x	x	x
Oxygen supply (l/min)	x	x	x	x	x	x	x
In patients requiring mechanical ventilation:							
FiO_2_	x	x	x	x	x	x	x
PEEP [mbar]	x	x	x	x	x	x	x
Body temperature	x	x	x	x	x	x	x
RRsys [mmHg]	x	x	x	x	x	x	x
RRdia [mmHg]	x	x	x	x	x	x	x
Mean arterial pressure [mmHg]	x	x	x	x	x	x	x
Heart rate [1/min]	x	x	x	x	x	x	x

